#### Sample Size

The statistical program G*Power was used to conduct power analysis. With 2 groups (intervention and control), 3 measurements (baseline, time 1, and time 2), an assumed correlation among repeated measures of 0.3, and a small-medium effect size and a power of 0.8, the recommended sample size for repeated measures analysis of variance (ANOVA) was 102. Sample size calculations were made considering attrition rates (approximately 20%) observed in similar studies using mobile technology interventions with cancer survivors [24].

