### Procedure

A flow diagram of the progress through each phase of this 2-group parallel randomized trial is presented in Figure 2. A total of 123 eligible participants attended baseline assessments. Participants were randomized to the control or intervention arm. Of 123 participants, 62 assigned to the intervention group were invited to attend a lifestyle information and education session where they would also receive their Fitbit activity monitor, and 55 were able to attend. During the lifestyle information and education session, each participant was provided with a Fitbit Alta. The Fitbit activity tracker was set up and paired with the participants’ mobile device. The participant was given an information sheet with instructions on how to synchronize their Fitbit device and app and asked to perform this weekly.

The remaining 61 participants assigned to the control group were invited to an appointment where they would be provided with a Fitbit activity monitor, and 53 were able to attend. During this meeting, each participant was provided with a Fitbit Flex 2. The Fitbit was paired with the participants’ mobile device. The participant was given an information sheet with instructions on how to synchronize their Fitbit and asked to perform this weekly or at least once a month to prevent loss of data.

All participants wore a Fitbit® activity monitor for the 6-month duration of the study. Participants in the intervention group received weekly personalized SMS text messages, including feedback on their physical activity level and a personalized physical activity goal each week for 8 weeks.

All participants were invited to a postintervention assessment (12 weeks later) to determine efficacy of the lifestyle information and education session and personalized goal setting mHealth intervention for increasing physical activity and improving clinical and psychological outcomes.

All participants continued to wear Fitbit for the remainder of the study, but the personalized goal setting intervention had ceased after 12 weeks. To determine if any effects of a lifestyle information and education session and personalized goal setting mHealth intervention were maintained 3 months later, all participants were invited to a follow-up assessment (6 months after baseline assessment).

At the conclusion of the study, all participants in the intervention group were invited to be interviewed about their experience of the Moving On program, and 13 interviews were conducted.

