### Statistical Analysis

To maximize power and conform to intention-to-treat analysis, missing data will be handled using multiple imputation methods (ie, the expectation-maximization algorithm) if assumptions regarding mechanisms of missingness are met.

A series of 3 (baseline, T1, and T2) × 2 (control and intervention) mixed ANOVAs will be performed to determine the efficacy of a lifestyle information and education session and goal setting mHealth intervention on clinical, psychological, and health behavior measures.

Independent sample *t*-tests will be used to analyze group differences (control and intervention) in average daily step count across the 24 weeks of the study.

Thematic analysis of interview transcripts will be used to explore the acceptability of the Moving On program for recipients.

Quantitative data will be analyzed with IBM SPSS Statistics 24. NVivo 12 will be used to facilitate organization and analysis of qualitative data.

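### The 3 × 2 mixed ANOVA treats the pre-randomization baseline as an outcome, so its group-by-time test is valid but inefficient, and sensitive to the baseline BMI gap

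*Protocol article*

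**What the plan says.** The Statistical Analysis section fixes the layout: "A series of 3 (baseline, T1, and T2) × 2 (control and intervention) mixed ANOVAs will be performed". The same sentence makes these models the efficacy analysis ("mixed ANOVAs will be performed to determine the efficacy of a lifestyle information and education session and goal setting mHealth intervention") and gives their scope: "goal setting mHealth intervention on clinical, psychological, and health behavior measures". The one exception is Fitbit step count, which is compared by independent-sample t-tests and is outside this point. No covariate is named, and the text does not say whether the group main effect or the group-by-time interaction is the efficacy test.

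Study Design places the baseline assessment before randomization. The Sample Size section uses two groups, three measurements, "an assumed correlation among repeated measures of 0.3", and "a small-medium effect size and a power of 0.8", and arrives at 102.

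The Procedure section poses two questions: efficacy at 12 weeks, and a later assessment "To determine if any effects of a lifestyle information and education session and personalized goal setting mHealth intervention were maintained 3 months later".

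Table 4 gives baseline BMI as 32.64 (SD 5.41) in control and 30.33 (SD 3.99) in intervention, P = .01.

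**The concern.** A measurement taken before randomization cannot respond to treatment. Entered as an outcome level, it leads to two quite different tests. The interaction compares change from baseline, which subtracts the whole baseline value where only a fraction r of it is predictive. The group main effect averages baseline into the outcome, so a baseline gap becomes part of the apparent effect.

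Two things are at stake. One is power, which the same section says it wants to maximize. The other is the reading of BMI, where the arms differ at baseline: an unadjusted change analysis invites regression to the mean in one direction, and a main effect carries the gap forward in the other. In addition, a 2-df omnibus interaction does not by itself estimate either the T1 or the T2 effect that the Procedure section asks about.

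**Working it through.** **1. Which test the trial was sized on.** The effect size has no number and alpha is not stated, so f = 0.15 and alpha = 0.05 are assumptions. For the interaction, λ = f²·N·m/(1 − r) = 0.15² × 102 × 3/0.7 = 9.84 on 2 and 200 df, which gives power 0.802. So 102 is reproduced. The between-group test gives 108 at f = 0.20 and reaches 102 only at f = 0.205. The sizing therefore points to group × time.

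**2. Variances of the arm contrast.** Units are σ², with compound symmetry and r = 0.3 from the Sample Size section.

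- Single visit, change: 2(1 − r) = 1.40
- Single visit, baseline-adjusted: 1 − r² = 0.91
- T1/T2 mean, change: (1 + r)/2 + 1 − 2r = 0.65 + 0.40 = 1.05
- T1/T2 mean, baseline-adjusted: (1 + r)/2 − r² = 0.65 − 0.09 = 0.56

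Information lost without adjustment is 1 − 0.91/1.40 = 35% at one visit and 1 − 0.56/1.05 = 47% for the mean. For the mean, the loss is 1 − 0.50/0.75 = 33% at r = 0.5 and 1 − 0.14/0.15 = 7% at r = 0.9.

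**3. Power for an illustrative effect of 0.40 SD**, equal at T1 and T2. This effect is assumed, not taken from the article. There are 51 per arm (102/2), two-sided 0.05, and SE = √(2v/51).

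| Test | v | 0.40/SE | Power |
|---|---|---|---|
| One visit, change | 1.40 | 1.71 | 39% |
| One visit, adjusted | 0.91 | 2.12 | 55% |
| T1/T2 mean, change (1 df) | 1.05 | 1.97 | 50% |
| T1/T2 mean, adjusted (1 df) | 0.56 | 2.70 | 76% |

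The 2-df interaction has λ = (102/4) × 0.40² × (2/3)/0.7 = 3.89 and power 40%. Of the 36 points between 40% and 76%, about 10 come from using 1 df instead of 2, and the rest from adjustment.

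**4. Baseline BMI gap.** Table 4 covers 53 control (49 + 4) and 54 intervention (42 + 12) participants, 107 in all. The pooled SD is √[(52 × 5.41² + 53 × 3.99²)/105] = 4.75. The gap is 2.31 kg/m², or 2.31/4.75 = 0.49 SD.

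**5. Effect of that gap on the interaction, with no treatment effect.** The change contrast shifts by 2.31(1 − r): 1.62 kg/m² at r = 0.3, 1.16 at 0.5 and 0.23 at 0.9. Control starts higher and is expected to fall more, so the shift goes against the intervention. Simulating the full 3 × 2 ANOVA with the baseline gap held at its Table 4 value gives rejection in about 25–27% of trials at r = 0.3, 19–20% at r = 0.5 and 8% at r = 0.9, where 5% is nominal.

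**6. Effect on the group main effect, if that were read.** The shift in the three-visit mean is 0.487(1 + 2r)/3 SD. The test's SE is √[(1 + 2r)/3] × √(1/53 + 1/54), and the critical value is 1.983. Given baseline, the statistic has SD √[2(1 + r − 2r²)/9]/√[(1 + 2r)/3].

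- r = 0.3: the statistic centers at 0.260/0.141 = 1.84 with SD 0.68, so it exceeds 1.983 about 42% of the time.
- r = 0.9: it centers at 0.454/0.187 = 2.43 with SD 0.26, so it exceeds 1.983 about 96% of the time.

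This error favors the intervention.

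**The case against.** The interaction is a valid test. Over repeated randomizations it is unbiased with correct size, and the rates in step 5 apply only conditionally on the gap seen. That stands. Table 4 also describes 107 of the 123 randomized, so part of the gap may have arisen after randomization. That stands too.

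A reader might infer that the plan throws away half its information on every outcome. The article does not support this. About half holds for a sustained effect averaged over two visits at r = 0.3. At one visit it is 35%, and for outcomes that track closely over time it is small. If BMI has a correlation near 0.9 (an assumption), the interaction loses about 7% and the regression-to-the-mean shift is only 0.23 kg/m².

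A reader might also infer that BMI will almost certainly appear to improve with no treatment effect. That follows only if the group main effect is taken as efficacy. The article never says so, and its sample size fits the interaction.

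Follow-up contrasts, confidence intervals and covariate lists are often left to a separate analysis plan, and a mixed ANOVA does not rule them out. Their absence is therefore not the finding. What remains is a stated choice: baseline is fixed as an outcome level in the efficacy model.

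**Conclusion.** The point holds as one of efficiency and conditional bias, not invalidity. At the plan's own correlation of 0.3, leaving baseline unadjusted costs 35% of the information at one visit (power 39% against 55% at 0.40 SD) and 47% for the T1/T2 mean (50% against 76% with 1-df tests on both sides). The cost shrinks as the correlation rises.

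For BMI, the observed gap inflates false rejection by the interaction to about 25–27%, 19–20% and 8% at correlations of 0.3, 0.5 and 0.9. The main effect would be far worse (42% at 0.3, 96% or more from 0.9 upward), which is reason enough to rule it out in writing.

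These figures assume compound symmetry, alpha 0.05 and, for power, 51 per arm. The true correlation for BMI is not given. The false-rejection rates are specific to BMI: the Table 4 weight gap is only 2.92 kg (0.19 SD), and no baseline means are shown for the other outcomes.

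**What to change.** Replace the mixed ANOVA with a mixed model on T1 and T2 containing arm, visit, arm × visit and baseline value × visit, or with a constrained longitudinal model with equal baseline means. Name the arm contrast at T1 as efficacy and the arm contrast at T2 as maintenance, each with a 95% CI. State that efficacy will not be read from the main effects of group or time. The gain to expect for these contrasts is the single-visit one (39% to 55% in the example), not the larger gain for the T1/T2 mean.

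Adjustment for age and sex, which also differ in Table 4, belongs in a secondary or sensitivity analysis, disclosed as chosen after the baseline table was seen.

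The cost is wording and syntax, since the baseline values are already collected. It is not free of consequence: the Results section says data collection is complete and analysis is underway, so the report must disclose that the model was changed after data collection ended.

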## Results

The recruitment for this study commenced in December 2017 and data collection began in January 2018. Data collection was completed by September 2018, and analysis is underway. Results are expected to be submitted for publication in winter 2019.

## Discussion

This protocol describes an RCT designed to evaluate the efficacy of an intervention using mobile technology and BCTs to improve health and well-being outcomes in a sample of cancer survivors with a BMI of 25 kg/m^2^ or greater. Strengths of the study protocol include a description of the intervention content in terms of a standardized list of BCTs [13] and the MOD taxonomy [23], as well as a description of control condition content using the same standardized descriptors. Qualitative elements examining the acceptability of the intervention are an additional strength of the study.

Cancer survivors require additional support to self-manage lifestyle behaviors. mHealth technology may provide a cost-effective solution within modern oncology care. However, there is limited evidence for the effectiveness of mHealth interventions for behavior change with cancer survivors. mHealth is a novel area of research, and although it holds enormous potential for improved health care delivery in the future, it currently lacks a strong evidence base [36]. This study evaluating the efficacy of an mHealth intervention using evidence-based BCTs to improve health and well-being outcomes in a sample of cancer survivors who are overweight represents an important contribution to the field. If results of the study find the *Moving On* program to be effective and acceptable to participants, possibilities for full-scale national roll-out will be explored.

The findings of this study will be of interest to health care professionals and patients, health psychologists with an interest in behavior change, and those developing new technologies to support health behavior change.

## Abbreviations

ANOVA: analysis of variance
BCT: behavior change technique
BCW: behavior change wheel
BMI: body mass index
EPIC: European Prospective Investigation into the Cancer and Nutrition
FFQ: Food Frequency Questionnaire
mHealth: mobile health
MOD: mode of delivery
RCT: randomized controlled trial
SMS: short message service
